Gynoflor  is a vaginal ovule containing at least 107 colony forming units of live Lactobacillus acidophilus, 0.03mg oestriol and 600mg lactose, manufactured and distributed in Europe by Medinova of Switzerland. The company-manufactured placebo preparation is identical to the study intervention, apart from containing no lactobacillus or oestriol.  Gynoflor and placebo will be provided free of charge. The Australian Therapeutic Goods Administration (TGA) uses the Clinical Trial Notification (CTN) Scheme to administer the use in clinical trials of products not currently entered on the Australian Register of Therapeutic Goods. 2% clindamycin cream is available in Australia and registered with the TGA for use in BV. 

The specific trial design has been developed to accommodate the different formulations and the differing durations of therapy of the two interventions being tested, while maintaining blinding of participants, researchers and clinicians. Importantly, it will be explained to all participants that they will receive either a vaginal cream or ovule for 7 or 12 days, but participants will not be informed whether clindamycin, Gynoflor or the placebo is in ovule or cream form to maintain blinding. 

Women will be instructed to use all vaginal treatments during menstrual periods.  When menses are particularly heavy, they may choose to omit vaginal therapy those days, but to ultimately take the full treatment regimen.  This information will be carefully recorded in addition to self-reported adherence. 

Participants
Women will be recruited for this study from the Melbourne Sexual Health Clinic (MSHC). The MSHC is the largest sexual health service in Victoria, and diagnoses 450 cases of BV annually. We have recently conducted successfully a 2 year longitudinal study of BV at MSHC [18].
  
Women will be eligible women if they are
·	pre-menopausal (18-45 years of age)
·	able to provide informed consent in English. 
·	have symptomatic BV defined by a Nugent score of 7-10 or 3-4 Amsel criteria with a Nugent score of 4-6. Nugent method is the standard diagnostic method for the diagnosis of BV. A Nugent score (NS) of 0-3 is classed as normal flora, 4-6 as intermediate flora and 7-10 as BV.
Exclusion criteria:
·	pregnancy
·	known HIV positive status
·	oestrogen-dependent tumors (breast, uterus, vagina)
·	abnormal vaginal bleeding of unknown aetiology
·	hypersensitivity or allergy to metronidazole, clindamycin or any of the ingredients of Gynoflor

Procedures

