All women attending MSHC with vaginal symptoms are assessed for BV using the Nugent method by clinicians as part of their standard care. MSHC has an electronic alert that will trigger whenever clinicians enter the diagnosis of BV into the computerised record, to remind them to offer enrolment in the study to eligible women.  If a woman is interested in participating in the trial, informed consent will be sought by the designated research nurse, who will have been trained in this procedure.

Enrolled women will be randomised to one of the three arms of the study in equal proportions (one third in each arm) using a computer-generated randomisation sequence (see below). A computerised script will be sent to the on-site pharmacy where the treatment kit will be collected by the participant. The contents of the kit will be packaged so as to preserve blinding of clinic staff. Clear instructions on the administration of the oral and vaginal preparations and durations of therapy for each individual will be inside each kit. The participant will collect this kit from pharmacy staff at the end of the visit just prior to departure. Importantly, participants, clinicians and pharmacy staff will not be aware to which arm the participant has been allocated at enrolment. Participants will be reviewed and examined 7-14 days following completion of therapy. It is possible that women may inform a practitioner that they had used a vaginal ovule or cream, potentially identifying the clindamycin arm only but not differentiating between the probiotic and placebo. Due to this small risk of unblinding, assessment of the major trial outcome of BV will only be made using a laboratory diagnosis, as outlined below, not a clinical diagnosis. Laboratory staff, who do not have access to the clinical history, will score vaginal flora (the outcome measure for the study), therefore maintaining blinding. 

Visit procedures
Visit one (at enrolment);

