All participants will have a clinical history taken and undergo speculum vaginal examination, including pH estimation (Spezialindikator strips pH 2-9, Merck & Co., NJ, USA).  After explanation of the trial, women will be invited to participate and to provide written informed consent. Participants will then be asked to complete a questionnaire (regarding behavioural practices, risk factors for STIs, symptomatology {rating scale 1-5}, previous BV episodes and prior treatments). The clinicians will complete a pre-formatted data collection sheet on examination findings (e.g. presence of discharge, nature of discharge), genital specimens will be collected for vaginal microscopy, Chlamydia trachomatis PCR, Neisseria gonorrhoeae culture, and Trichomonas vaginalis culture, and a separate vaginal swab will be stored at -70oC for later analysis.  Following randomisation, study medication will be dispensed as outlined.  

Follow up at 4, 8 weeks, 12 weeks and 6 months
Kits containing a questionnaire, vaginal swab, glass slide, instructions for self-collection, and a prepaid envelope, will be used to examine BV recurrence and factors associated with recurrence at 4, 8 weeks, 12 weeks and 6 months following treatment. The first kit for the 4 week follow-up will be given to participants at the enrolment visit, at which point clear verbal and written instructions will be also be provided and participants given the opportunity to clarify any concerns. Kits for follow-up at 8, 12 weeks and 6 months will be posted to participants. At each follow-up point, participants will be asked about sexual and contraceptive practices, genital symptoms, oral and vaginal self-treatments, and clinician-prescribed therapies. They will self-collect a vaginal swab and make a smear on a glass slide, and return the swab, slide and questionnaire in the prepaid envelope (18). Reminders in the form of telephone calls, letters or SMS text-messages will be sent once she has received the kit by post and weekly after the due date for four weeks. If no specimens are received by this time, the woman will be classified as a non-responder for that interval. Non-responders will still be contacted at the subsequent follow-up point(s). 

Interval BV symptoms and unscheduled visits

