Women will receive a card and refrigerator magnet with the free call study telephone number, which will be staffed by the study nurse and research investigators. Participants will be encouraged to call the number if they have symptoms of BV during the study or concerns regarding treatment or possible side effects. A sample kit will be supplied to women so that if they are unable to attend MSHC they will be able to self-collect samples for interval symptoms after discussion with the research nurse. Women will be asked in the initial consenting process to allow any results from outside clinics for investigation of BV symptoms to be made available for the study. 

These procedures are similar to those we have previously used in the study of BV recurrence (18,36) and the trial of probiotics for vaginal candidiasis (38).  Only 3/130 and 3/287 women attended outside clinics in these studies as a result of providing easy and rapid review if a woman developed interval symptoms.

Stored samples
With participant consent, vaginal swabs will be stored at -80oC for future examination for potential pathogens. DNA will be extracted using the Magnapure system: MagnaPure LC (Roche Molecular System, Alameda, CA, USA) in accordance with manufacturer's protocol, followed by detection of potential pathogens using molecular amplification technology. 

Study Outcome Measures
Primary outcome measure
Recurrence of BV within 6 months will be defined as a Nugent score of 7-10. We have chosen 6 months rather than 12 months, based on our experience of relapse rates in our previous studies of BV (Figure1). Relapse of BV plateaus by 6 months. Additionally, compliance with follow up will be higher with a 6 month compared to 12 month follow up. 

Secondary outcome measures
1.	Recurrence of abnormal flora within 6 months will be defined by a Nugent score 4-10. 
2.	Behavioural practices and other factors (eg contraceptive use, past history of BV, smoking)  associated with BV recurrence.

Validation of primary outcome
All slides will be stored and re-scored by two independent experienced microbiologists blinded to the intervention group of the participant.  If slides vary in their Nugent score groupings (0-3, 4-6 and 7-10), our experienced laboratory staff will reach consensus using methods from our previous studies of BV recurrence (18, 36). 

Sample size calculation

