Major anticipated confounding factors and how these will be handled
By measuring all known factors that can influence the development and recurrence of BV at baseline, and ensuring an adequate sample size, this RCT should be able to account for all known and unknown confounders.

Details of contingencies:
Participants will be counselled at recruitment regarding the potential side effects of all medications being used. This verbal information will be reinforced with written information about possible side-effect and how to manage them. All participants will be provided with a card which lists the free study telephone number to call during office hours and will connect to an investigators' mobile number after hours. Finally, participants will be informed to stop using any study medications that they feel may be causing an adverse event, if they are unable to contact a researcher to discuss. 

Details of handling of adverse events:
Serious adverse events with any of the study medications are extremely unlikely, as all medicines being tested have histories of safe usage, including Gynoflor , which is available over-the-counter in Europe. For this reason, a data monitoring and safety committee will not be formed for this study. Anticipated side effects from the antibiotics are likely to be mild and to include symptoms such as nausea, headache, heartburn, diarrhoea, vaginal discharge or a metallic taste. Side-effects of Gynoflor include local irritation and burning, and vaginal discharge.  Any serious adverse event is very unlikely; however, as stated above all participants will be given clear printed instructions on a card with 9am to 9pm daily contact details. Women will be provided with their results by study investigators and if treatment of BV is required during follow-up prompt review will be arranged with a sexual health physician at Melbourne Sexual Health Centre. All clinicians at this service are highly experienced in the management of BV. Serious adverse or unforeseen events will be managed by referral of the participant to the appropriate professional for assessment and management and will be reported to the relevant ethics committee, VMIA (Victorian Managed Insurance Authority) and the TGA.

Details of methods to ensure confidential handling and storage of records:

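### Entry admits Nugent 4-6 as BV, but the primary event is Nugent 7-10 and needs no prior clearance, so non-response is scored by entry route and persistence is counted as recurrence

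*Protocol*

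**What the plan says.** **Entry.** Under Participants, women are eligible if they "have symptomatic BV defined by a Nugent score of 7-10 or 3-4 Amsel criteria with a Nugent score of 4-6". The same bullet adds: "A Nugent score (NS) of 0-3 is classed as normal flora, 4-6 as intermediate flora and 7-10 as BV". Intermediate flora with enough clinical signs is thus BV for admission but not on the laboratory scale.

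**Outcomes.** Under Study Outcome Measures, the primary reads "Recurrence of BV within 6 months will be defined as a Nugent score of 7-10" and the first secondary reads "Recurrence of abnormal flora within 6 months will be defined by a Nugent score 4-10". Neither mentions the baseline score or an intervening normal smear.

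**Why clinical signs are left out.** Procedures notes that the cream could reveal the clindamycin arm, so "assessment of the major trial outcome of BV will only be made using a laboratory diagnosis, as outlined below, not a clinical diagnosis".

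**Timing.** Procedures also states: "Participants will be reviewed and examined 7-14 days following completion of therapy". No smear is specified for that review, and it has no role in establishing cure. Under the follow-up heading, the home-collection kits "will be used to examine BV recurrence and factors associated with recurrence at 4, 8 weeks, 12 weeks and 6 months following treatment".

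**Retreatment.** The section on handling adverse events says that "if treatment of BV is required during follow-up prompt review will be arranged". The outcome definitions do not say how such treatment counts.

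**Purpose.** The primary aim is about recurrence at six months; hypothesis 2 is about rates of cure.

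**The concern.** The state that qualifies some women for the trial is not a state that the primary outcome can register. Two women who both fail to respond are scored differently according to how they entered. If a woman's 4-6 presentation returns and is treated, no primary event is recorded, and the treatment may make a later 7-10 less likely.

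Separately, an event may be disease that never cleared or disease that came back. A better initial cure and better prevention of relapse are different conclusions. The outcome as worded cannot tell them apart, yet it carries the name of only one.

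At stake are some power, because part of each arm may contribute little to the contrast, and the meaning of a positive or negative result.

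**Working it through.** **1. Definitions side by side.** Take women whose score never changes through 4, 8 and 12 weeks and 6 months.

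| Entry state | Primary (7-10) | Secondary (4-10) |
|---|---|---|
| Nugent 7-10, unchanged | event | event |
| Nugent 4-6 with 3-4 Amsel criteria, unchanged | no event | event at week 4 |
| Nugent 4-6, later rises to 7-10 | event | event |

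The anomaly is confined to the middle row. No statement elsewhere in the protocol handles those women separately.

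**2. The protocol's own sample size.** Inputs from Sample size calculation: 50% v 30%, power 90%, alpha 0.05 (sidedness not stated; two-sided reproduces the figure).

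n = [1.960·√(2·0.4·0.6) + 1.2816·√(0.5·0.5 + 0.3·0.7)]² / 0.20² = (1.358 + 0.869)² / 0.04 ≈ 124 per arm, against the stated 123. The figure reproduces and is not in dispute.

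Recruiting 150 per arm with 20% loss leaves 150 × 0.8 = 120 evaluable. Power = Φ{[d − 1.960·√(2p̄(1−p̄)/n)] / √[(p₁(1−p₁) + p₂(1−p₂))/n]}. With n = 120 and 50% v 30% this is Φ[(0.200 − 0.124)/0.0619] = 0.890.

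**3. Illustrative dilution.** Let f be the share entering at 4-6 and r their control-arm rate of reaching 7-10. Neither is in the protocol; I assume f = 5-20% and r = 20-30%. The stated 50% and 30% are applied to the 7-10 entrants.

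- Control rate: p₁ = 0.5(1−f) + f·r
- Case A, no treatment effect in 4-6 entrants: p₂ = 0.3(1−f) + f·r
- Case B, the protocol's ratio 30/50 = 0.6 applies to them: p₂ = 0.3(1−f) + 0.6·f·r

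Example, case A, f = 10%, r = 30%: p₁ = 0.48, p₂ = 0.30, difference 0.18, power = Φ[(0.180 − 0.1234)/0.0619] = 0.82.

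| f | Case A: difference | Case A: power | Case B: difference | Case B: power |
|---|---|---|---|---|
| 0 | 20 points | 89% | 20 points | 89% |
| 5% | 19 | 86% | 19.4-19.6 | 87-88% |
| 10% | 18 | 82% | 18.8-19.2 | 86-87% |
| 20% | 16 | 73-74% | 17.6-18.4 | 82-84% |

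Ranges within a cell come from r = 20% to 30%.

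**4. Persistence against relapse.** A score of 7-10 at the first kit, at 4 weeks, is an event whether or not the flora ever normalised. The protocol gives no figure from which the split can be calculated.

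**The case against.** The strongest reply has four parts.

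- **Laboratory-only outcome.** The protocol gives a sound reason: the cream could unblind clinicians. That stands as the reason for leaving Amsel criteria out of follow-up. It does not explain the mismatch with entry.
- **Nested thresholds.** A 4-10 secondary around a 7-10 primary is legitimate, and any woman at 4-6 in follow-up differs on the two by design. That also stands; the disagreement between the two outcomes is not itself the defect.
- **Counting every 7-10 after treatment.** This is the sound intention-to-treat endpoint. I agree, which is why the remedy changes its name and reporting rather than the event.
- **The power figures.** They rest on assumed inputs. The 50% is stated for the placebo arm as recruited, so lowering it again for 4-6 entrants may count them twice. This is fair, and the figures show only a possible range.

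The protocol also allows sampling for interval symptoms and asks about prescribed and self-treatment, so a symptomatic relapse at 7-10 can be captured and retreatment is recorded. What is missing is a rule for how retreatment counts.

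Some of the remedy could sit in an analysis plan that is not shown. The entry and outcome definitions, however, are fixed in the protocol, and the mismatch arises there.

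**Conclusion.** The point holds in limited form. Entry is wider than the primary event, and neither recurrence definition requires clearance. The consequences are some dilution and an unclear claim. Power could be one or two points lower if few women enter at 4-6 and they respond like the others. It could be about 16 points lower (89% to 73%) if a fifth enter that way and treatment does nothing for them. Both ends rest on assumed shares and rates.

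Three stronger readings are not supported:

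- **That 4-6 entrants cannot fail on the primary outcome.** They can, by reaching 7-10; only failure by staying at 4-6 goes unseen.
- **That the comparison is biased between arms.** Allocation is random in equal proportions, so these women are balanced on average.
- **That the background one-month cure rates of 70-90% give the fraction of events that are non-clearance.** The definition of cure behind those rates is not shown, one-month failure mixes non-clearance with early relapse, and not every failure need score 7-10.

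**What to change.** - Keep all randomised women in the intention-to-treat analysis. Adjust the between-arm comparison for baseline Nugent category (7-10 v 4-6) and report results by category. With an assumed share of 5-20%, the 4-6 group would be 6-24 women per arm (0.05 × 120 to 0.20 × 120), so its results are descriptive. Adjustment makes the dilution visible; it does not restore the lost power.
- Name both outcomes persistence or recurrence, of BV and of abnormal flora, and align the wording of the aim and hypothesis 2.
- Report by arm how many events were already present at the first post-treatment sample, and state which sample that is. The first one specified is at 4 weeks, so this count bounds non-clearance rather than measuring it.
- Add a sensitivity analysis that counts retreatment for BV as an event.

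Do not count abnormal flora only after a post-treatment score of 0-3. That would condition on a result arising after randomisation and weaken the randomised comparison.

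The baseline score comes from microscopy at enrolment, and treatments are already asked about at each follow-up. No new visit, sample or participant is needed; the cost is revised wording and a little more analysis work.

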The primary aim of this study is to determine if the use of combination oral metronidazole and vaginal clindamcyin therapy and/or the combination of oral metronidazole with vaginal probiotic/oestrogen therapy is associated with lower recurrence rates of BV at six months than the current recommended therapy for BV oral metronidazole alone.
Secondary aims are to investigate behavioural practices and other factors associated with BV recurrence following therapy.

Hypotheses
1.	Combination antibiotic therapy of oral metronidazole with vaginal clindamycin will be more effective than mono-therapy in the treatment of bacterial vaginosis.
2.	Restoring local vaginal flora and an acidic vaginal pH through replacement of Lactobacillus spp and topical oestrogen (in addition to oral metronidazole), will achieve higher rates of cure than current recommended therapy oral metronidazole alone.

Study design
Randomised double-blind placebo controlled trial for treatment of BV with 3 arms: oral metronidazole/vaginal placebo; oral metronidazole/vaginal clindamycin; and oral metronidazole/vaginal probiotic Gynoflor (Lactobacillus species and oestriol). 

Intervention
This trial has been designed so that all participants receive standard first-line therapy for BV in Phase 1 – i.e. 7 days of oral metronidazole (see table below). 

Intervention	Phase 1: Oral treatment 	Phase 2: Vaginal treatment 	Phase 3: follow up	
Arm one	Metronidazole 	Clindamcyin 	Follow up at 1, 2, 3, and 6 months	
Arm two 	Metronidazole 	Gynoflor 		
Arm three	Metronidazole 	Placebo 		

In Phase 2, the vaginal phase, to be undertaken concurrently with Phase 1, one third of participants will be randomised to receive 7 days of vaginal clindamycin cream (2%), one third will receive 12 days of a vaginal probiotic ovule Gynoflor, and one third will receive a vaginal placebo ovule (12 days of the placebo ovule). This is a double-blinded trial and neither interventions nor placebo will be identifiable by their packaging. 

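### Follow-up is timed from the end of treatment, which nominally falls 5 days earlier in the clindamycin arm, so the review window differs by arm, the kit dates are ambiguous, and scheduling can disclose course length

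*Protocol*

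**What the plan says.** The Intervention section of the Protocol gives every woman 7 days of oral metronidazole and starts the vaginal course alongside it: "In Phase 2, the vaginal phase, to be undertaken concurrently with Phase 1". The vaginal courses differ in length: "one third of participants will be randomised to receive 7 days of vaginal clindamycin cream (2%), one third will receive 12 days" of Gynoflor, and for the rest "one third will receive a vaginal placebo ovule (12 days of the placebo ovule". A woman with heavy menses may delay doses: "they may choose to omit vaginal therapy those days, but to ultimately take the full treatment regimen".

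Three statements fix follow-up, and they do not share a stated origin:

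- Procedures, for the clinic review: "Participants will be reviewed and examined 7-14 days following completion of therapy".
- Follow up at 4, 8 weeks, 12 weeks and 6 months, for the self-collected swab kits, which are used to examine recurrence and "factors associated with recurrence at 4, 8 weeks, 12 weeks and 6 months following treatment".
- The design table under Intervention, which lists months 1, 2, 3 and 6 with no starting point.

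On blinding, the Blinding section covers participants, investigators, research staff, treating clinicians and those who read the specimens. Procedures puts each woman's instructions and duration of therapy inside the kit. The same section accepts that a woman might mention a cream or an ovule, which could identify the clindamycin arm. For that reason it restricts the primary outcome to a laboratory diagnosis made without the clinical history.

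**The concern.** A schedule that starts when treatment ends starts at a different point in each arm if the courses differ in length. All women stop metronidazole at the same nominal time. Under such a schedule, however, those on the 12-day ovule are assessed 5 days later after it than those on the 7-day cream. The placebo ovule contains no antibiotic, so a placebo woman has 5 more days without active treatment in which to relapse before she is assessed. That would tilt the clindamycin versus placebo comparison, one of the two primary comparisons, towards clindamycin.

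The second issue is operational. A review can be booked from the completion date only by someone who knows that date, and the date shows whether the course was 7 or 12 days. The plan keeps course length inside the kit to protect the blind, and then sets a review that depends on it.

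**Working it through.** The plan gives no figure for the timing itself, so there is none to reproduce. Its sample size of 123 per group is not in dispute (the usual two-sided pooled formula for 50% versus 30% at 90% power gives 124) and is used below only for scale.

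**Inputs.** Course lengths of 7 and 12 days, started together (Intervention). Review 7 to 14 days after completion (Procedures). Kits at 4, 8 and 12 weeks and 6 months after treatment (Follow up section). Control recurrence 50% and planned difference 20 points (Sample size calculation). Assumptions: treatment starts at once, no doses are delayed, and 6 months is 182 days.

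**Review window, in days from the start of treatment.**

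- Clindamycin: 7 + 7 = 14 to 7 + 14 = 21.
- Gynoflor and placebo: 12 + 7 = 19 to 12 + 14 = 26.
- Common to all arms: days 19 to 21. Days 14 to 18 fit only the cream and days 22 to 26 only the ovules.

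**Kit due dates, in days from the start of treatment.**

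| Reading of the kit origin | Clindamycin | Gynoflor, placebo | Offset |
|---|---|---|---|
| End of the oral course | 35, 63, 91, 189 | 35, 63, 91, 189 | 0 |
| Last vaginal dose | 35, 63, 91, 189 | 40, 68, 96, 194 | 5 days |

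The text does not choose between these rows. Five days is 5/28 = 18% of the 4-week interval and 5/182 = 2.7% of the six-month interval.

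**Size of a 5-day offset under the second reading.** Assume a constant hazard with 50% recurrence at 182 days: λ = ln 2 / 182 = 0.00381 per day, and recurrence by day t is 1 − exp(−λt).

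| Swab | t days | t + 5 days | Difference |
|---|---|---|---|
| 4 weeks | 10.1% | 11.8% | 1.7 points |
| 8 weeks | 19.2% | 20.7% | 1.5 points |
| 12 weeks | 27.4% | 28.8% | 1.4 points |
| 6 months | 50.0% | 50.9% | 0.9 points |

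**Sensitivity to the shape of the hazard.** The Background cites one-month cure rates of 70-90%. Taking the complement, 10-30%, as an assumed range for recurrence by 4 weeks, the 5-day shift at 4 weeks is 1.7 points (10%), 3.1 points (20%) or 4.3 points (30%). At six months the shift goes the other way. The Primary outcome measure section says relapse levels off by then. If the planning 50% at 6 months is joined to the 58% at 12 months from the earlier cohort (an assumption), five days add about (58 − 50)/182 × 5 = 0.2 points.

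**Effect on the test.** With 123 per group and 50% in both, the standard error of the difference is √(2 × 0.5 × 0.5/123) = 0.064. A shift of 0.0094 is 0.15 standard errors and moves a two-sided 5% test to about 5.2%.

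**Which comparisons are touched.** Gynoflor and placebo share the 12-day course, so their timing matches under either reading. Only comparisons with the clindamycin arm can be offset.

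**The case against.** The strongest reply is that the Procedures sentence governs the clinic review only. The primary outcome comes from the kits, and their wording can mean the 7-day oral course that all arms share, in which case the swabs are not offset at all. This stands. A reader might infer that every swab is certainly taken 5 days later in the ovule arms, but the text supports only an ambiguity.

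A reader might also infer that scheduling gives away each woman's allocation. It does not. Gynoflor and placebo cannot be told apart by duration, a review on days 19 to 21 fits all three arms, and doses delayed for menses blur the completion date. The plan has already conceded that the clindamycin arm may be identified and has answered with blinded laboratory scoring. What remains is that the schedule itself adds a route which the plan does not mention. It reaches staff who review women, take their histories and chase kits, not those who score slides.

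A third tempting reading is that the intention-to-treat analysis is breached. It is not: timing visits from the end of treatment neither drops nor reclassifies anyone, and the Data analysis section states no time origin for the survival curves.

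It is also fair to say that equal intervals after the last dose are a defensible aim, and that four weeks of reminders may spread actual swab dates by more than 5 days. Such spread, if similar in all arms, adds noise; a fixed offset by arm does not average out.

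**Conclusion.** The point holds in limited form. The review window differs by arm on the text as written: days 14-21 against 19-26, assuming doses are taken as scheduled. The kit origin is undefined for courses of unequal length. If it is the last vaginal dose, clindamycin versus placebo is slightly biased towards clindamycin: about 1.7 points at 4 weeks and at most about 0.9 at six months under the constant-hazard assumption, and perhaps 0.2 at six months if relapse plateaus. Against a planned difference of 20 points, this would not change the trial's conclusion on its own. Gynoflor versus placebo is unaffected, and the sample size does not change.

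Booking by completion date can disclose course length to staff meant to be blinded and so can identify the clindamycin arm. This adds modestly to a risk that the plan already accepts. The change is worth making because it is cheap, not because the bias is large.

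**What to change.** Time the post-treatment review, all four kits and the analysis clock from the date of randomisation, with the same calendar windows in every arm, and use that origin in the design table too. Record the date on which treatment was completed as data only, and state that it is not used to book reviews, set kit due dates or trigger reminders.

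The between-arm offset then becomes zero at every assessment, and nobody needs the course length to run the schedule. The route that the plan already concedes, a woman mentioning her cream or ovule, stays open and still relies on laboratory scoring.

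The cost is wording and due-date labels. The downside is that time since the last vaginal dose will differ by about 5 days between the cream and ovule arms, which should be acknowledged when early swabs are interpreted.

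### The protocol specifies no systematic elicitation of adverse effects and no tolerability outcome, so any comparison of tolerability by arm would rest on spontaneous reports and non-specific genital symptoms

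*Protocol*

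**What the plan says.** Only the protocol is at hand; a SAP has not been seen.

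- **Kits** (Follow up at 4, 8 weeks, 12 weeks and 6 months). The kits "will be used to examine BV recurrence and factors associated with recurrence at 4, 8 weeks, 12 weeks and 6 months following treatment". On content: "participants will be asked about sexual and contraceptive practices, genital symptoms, oral and vaginal self-treatments, and clinician-prescribed therapies".
- **Post-treatment review** (Procedures). "Participants will be reviewed and examined 7-14 days following completion of therapy". Nothing more is said about it. It has no entry under Visit procedures, and the table under Intervention lists follow-up at 1, 2, 3 and 6 months only.
- **Telephone line** (Interval BV symptoms and unscheduled visits). Women are "encouraged to call the number if they have symptoms of BV during the study or concerns regarding treatment or possible side effects".
- **Expected effects** (Details of handling of adverse events). For the antibiotics, "symptoms such as nausea, headache, heartburn, diarrhoea, vaginal discharge or a metallic taste"; for Gynoflor, local irritation, burning and discharge. Serious or unforeseen events are referred and reported. No recording of expected mild events is described.
- **Outcomes** (Study Outcome Measures). The primary outcome is a Nugent score of 7-10 within 6 months. The secondary outcomes are a Nugent score of 4-10 and factors associated with recurrence. The Data analysis section covers recurrence only.
- **Adherence** (Intervention). On vaginal doses left out during heavy menses: "This information will be carefully recorded in addition to self-reported adherence".

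**The concern.** The trial asks whether a second product should be added to standard metronidazole. That decision needs the harms of adding it as well as the reduction in recurrence.

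The question is open on the protocol's own account. It describes this as the first randomised trial of these combinations. Of the two Gynoflor trials it cites, one used no antibiotic and the other started Gynoflor two to seven days after the antibiotic ended, whereas here the two are given concurrently. The protocol also expects the combined oral and vaginal routes to keep systemic effects low, yet names no routine data item that would show whether they do.

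What is asked of participants is settled when the forms are written. A SAP can define how adverse effects are tabulated, but it cannot supply answers that nobody sought. Spontaneous reporting tends to miss mild effects, so rates may be understated in every arm and a real difference between arms may be hard to see.

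**Working it through.** **1. The plan's own figure.** The only sample-size figure is for efficacy: 123 per group for 50% v 30% recurrence, 90% power, alpha 0.05. A two-sided two-proportion formula with pooled variance gives 124, so the figure reproduces. This point does not depend on it. It supplies only the numbers per arm: 150 recruited, and 150 × 0.80 = 120 after the assumed 20% loss.

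**2. Each expected effect against each stated route.**

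| Expected effect | Kit questionnaires | 7-14 day review | Participant's call |
|---|---|---|---|
| Diarrhoea, headache, heartburn, nausea, metallic taste | Not a listed topic | Content undefined | Yes, if she calls |
| Discharge | Under genital symptoms, but also a BV symptom | Content undefined | Yes, if she calls |
| Local irritation, burning | Under genital symptoms, first asked 4 weeks after treatment | Content undefined | Yes, if she calls |
| Stopping because of an effect | Not a listed topic; adherence is self-reported, a reason is not mentioned | Content undefined | Yes, if she calls |

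The right-hand column is the only one in which side effects are expressly named.

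**3. Illustration of under-capture.** The protocol gives no side-effect rates and no reporting fraction, so both are assumed. With true rates p1 and p2, a fraction c of events reported equally in both arms, and n per arm, the recorded rates are c·p1 and c·p2. With two-sided alpha 0.05:

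power = Φ{ [ |d| − 1.96·√(2·m·(1−m)/n) ] / √( [a(1−a) + b(1−b)]/n ) }

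where a = c·p1, b = c·p2, d = b − a and m = (a + b)/2.

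For 10% v 20%, n = 150, c = 1: m = 0.15, the null SE is √(2 × 0.15 × 0.85/150) = 0.0412 and the alternative SE is √((0.09 + 0.16)/150) = 0.0408. Power = Φ[(0.10 − 1.96 × 0.0412)/0.0408] = Φ(0.47) = 0.68.

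| Fraction reported | Recorded rates | Power, n = 150 |
|---|---|---|
| 1.00 | 20% v 10% | 68% |
| 0.50 | 10% v 5% | 38% |
| 0.30 | 6% v 3% | 24% |
| 0.25 | 5% v 2.5% | 21% |

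With full capture but 120 per arm, power is 58%. For assumed true rates of 35% v 20% and 150 per arm, power is 83%, 47% and 25% at fractions of 1, 0.5 and 0.25.

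**The case against.** **The review of every woman.** A reader might infer that side effects reach the trial only through a phone call. The protocol does not support that. All participants are examined 7-14 days after therapy, and a clinician may well ask. What stands is that nothing says side effects are asked about or recorded there.

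**The topic list may be incomplete.** Self-reported adherence and the survey question that tests blinding are both collected, and neither appears among the kit topics. Absence from that sentence therefore does not prove that an item is absent from the forms, which are not shown. This is a fair limit on the finding. It does not supply a tolerability outcome or a stated point of elicitation.

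**Local effects are covered.** All arms take metronidazole, so its systemic effects are common background, and Gynoflor's listed effects are all genital. This partly stands: for Gynoflor the kits do touch the relevant effects. But discharge cannot be separated from recurrence, the first kit comes four weeks after treatment, and effects such as diarrhoea, which the protocol lists for the antibiotics, are not covered in the clindamycin arm.

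**Stopping is visible through adherence.** True of the fact of stopping, but no recording of the reason is described.

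**Leave it to the SAP.** A table by arm can be left there. The decision to ask cannot.

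**No monitoring committee.** The statement that "a data monitoring and safety committee will not be formed for this study" might be read as part of the fault. It is not: the protocol gives its reason, and a committee would not change what women are asked.

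**Conclusion.** The point holds as a gap in specified data collection. The protocol names no step at which every woman is asked about adverse effects, leaves the one suitable contact undefined, and lists no tolerability outcome. Systemic effects that it expects have no stated routine data item.

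It would go too far to conclude that tolerability cannot be compared. Genital symptoms, adherence, calls and whatever the 7-14 day review records would give some information. Under-capture weakens a comparison without making it impossible. Nor would full capture make the trial well powered for tolerability: under the assumed 20% v 10%, power is 58% to 68%.

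The fall to 38%, 24% or 21% at reporting fractions of 0.5, 0.3 and 0.25 rests wholly on assumed rates and on equal reporting in both arms. It shows direction and rough scale and is not an estimate for this trial. The primary efficacy analysis is untouched. This is a low-cost improvement worth making before recruitment starts.

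**What to change.** 1. Define the content of the 7-14 day review, list it under Visit procedures, and have every participant complete a fixed checklist there of the effects named under Details of handling of adverse events. Self-completion is preferable: the protocol recognises that a woman may mention cream or ovule to a practitioner, and these reports lack the protection of a laboratory-scored outcome.
2. Repeat the checklist in the 4-week questionnaire as back-up for women who miss the review.
3. On both forms, ask whether any study treatment was stopped and why.
4. Add a secondary outcome: adverse effects and treatment discontinuation by arm, in all randomised women.

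The cost is a slightly longer form and one extra table. No new visits are needed.
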